# Effect of interventions to reduce malaria incidence among military personnel on active duty: study protocol for a cluster randomised controlled trial of the impact of etofenprox-treated uniforms, permethrin-treated uniforms and DEET insect repellent

**DOI:** 10.1186/s13063-021-05801-9

**Published:** 2021-11-21

**Keywords:** Malaria, Insecticide-treated clothing, Military uniforms, Etofenprox, Permethrin, Cluster randomised trial, CRT, DEET, Repellent

## Abstract

**Background:**

While there is strong evidence that bite protection methods such as permethrin-treated clothing and topical insect repellents are protective against insect bites, there are few studies assessing the impact on malaria infection. This study will estimate the protective efficacy of treated uniforms and DEET insect repellent on the incidence of malaria infection among military personnel in an operational setting. Permethrin-treated uniforms used with DEET lotion will be compared to etofenprox-treated uniforms with DEET lotion. The effect of DEET lotion will be estimated by comparing permethrin-treated uniforms with DEET or placebo lotion.

**Method:**

A cluster randomised double-blind placebo-controlled trial is planned to evaluate the effectiveness of the interventions on preventing malaria infections in soldiers on active duty at Mgambo National Service Camp in Tanga, Tanzania. The arms are (1) permethrin-treated uniform with 30% DEET liposome formula; (2) permethrin-treated uniform with placebo lotion; (3) candidate insect repellent system, i.e. etofenprox-treated uniform with 30% DEET liposome formula; and (4) placebo, i.e. untreated uniforms with placebo lotion. The primary outcome is the incidence of *Plasmodium falciparum* malaria infection detected by polymerase chain reaction (PCR) by active case detection using surveys every 2 weeks for 12 months. Rapid diagnostic tests will be used for the diagnosis of participants with symptoms.

The unit of randomisation will be combania: companies formed by recruits aged 18 to 25 years; combania do activities together and sleep in the same dormitory. Unequal randomisation will be used to optimise statistical power for the primary comparison between permethrin-treated uniforms with DEET and etofenprox-treated uniforms with DEET.

**Discussion:**

This trial will provide the estimate of the effects of permethrin with DEET compared to those of the new fabric treatment etofenprox with DEET and any additional effect of using DEET. The results will inform strategies to protect military personnel and civilians who have more outdoor or occupational malaria exposure than the general public.

**Trial registration:**

ClinicalTrials.govNCT02938975.

**Supplementary Information:**

The online version contains supplementary material available at 10.1186/s13063-021-05801-9.

## Administrative information

Note: the numbers in curly brackets in this protocol refer to SPIRIT checklist item numbers. The order of the items has been modified to group similar items (see http://www.equator-network.org/reporting-guidelines/spirit-2727-statement-defining-standard-protocol-items-for-clinical-trials/).

## Introduction

### Background and rationale {6a}

People who live or temporarily stay away from permanent housing can be exposed to malaria vectors outdoors [1]. These people include military personnel on active duty [2, 3], residents and workers in the forests of South America [4] and Southeast Asia [5], migrants [6, 7] and displaced populations [8]. In addition to long-lasting insecticide-treated nets (LLINs) and indoor residual spraying (IRS), measures used to tackle vector-borne disease in these special populations include chemoprophylaxis, mass drug administration (MDA) [9] and mosquito bite prevention [10].

Means of bite prevention include repellents, which are applied to the skin (topical repellents) or to an area through volatilisation (spatial repellents) [11] and insecticide-treated clothing [12]. The most common active ingredient (AI) used to treat clothes, including uniforms, is permethrin [12]. Recently, etofenprox has become available. Etofenprox has a better human safety profile and is wash resistant up to 70 washes [13], providing prolonged protection. Permethrin and etofenprox function by irritating mosquitoes and other arthropods so that they do not bite through clothing [14]. DEET (*N*,*N*-diethyl-meta-toluamide) interferes with insect host location [15] and is the most effective available broad-spectrum topical insect repellent [16]. It has an excellent safety profile and has been in use for over 60 years [15]. It is applied directly to uncovered areas of the skin.

While there is very strong evidence that repellents and treated clothing are effective in reducing bites from biting arthropods [17], a recent systematic review found no evidence that topical repellents prevent malaria, insufficient evidence that spatial repellents prevent malaria and limited evidence that permethrin-treated clothing prevents malaria [18]. Two randomised control trials (RCTs) were included in the review; the evidence from them was deemed to be of low certainty due to the size and conduct of the studies. These studies were conducted in specific populations in Colombia (military personnel) and Pakistan (Afghan refugees). Insecticide-treated clothing may have a protective effect against clinical malaria caused by *Plasmodium falciparum* (risk ratio 0.49; *95% CI* (0.29–0.83)) and *P. vivax* (risk ratio 0.64; *95% C*I (0.40–1.01)) [18]. Therefore, World Health Organization (WHO) guidelines do not recommend insecticide-treated clothing for day-to-day use by the general population, although it may be beneficial as an intervention to provide personal protection against malaria in specific population groups [19].

In the case of military uniforms, the surface area of skin protected by DEET is small compared to that protected by clothing, limited to the hands, neck and face, and it is likely that the additional DEET provides only minimal additional protection. Furthermore, daily compliance with repellents as required for optimal disease prevention is rarely met, even for short periods of time [20]. It is therefore useful to estimate the protection provided by DEET in addition to treated uniforms to evaluate its utility and cost-effectiveness.

This study will evaluate the effectiveness on the incidence of malaria infection detected by polymerase chain reaction (PCR) of permethrin-treated and etofenprox-treated uniforms alone and in combination with DEET. We will also evaluate adherence to the interventions.

### Objectives {7}

#### Primary objective

To estimate the effect of etofenprox- compared to permethrin-treated uniforms by comparing etofenprox-treated uniforms (ETUs) plus DEET lotion compared to permethrin-treated uniforms (PTUs) plus DEET lotion on the incidence of *Plasmodium falciparum* malaria confirmed by polymerase chain reaction (PCR)

#### Secondary objectives

To estimate the protective efficacy of DEET lotion by comparing PTUs with DEET lotion to PTUs with placebo lotion on the incidence of PCR-detected *Plasmodium falciparum* malaria infectionTo estimate the protective efficacy of PTUs plus placebo lotion compared to untreated uniforms and placebo lotion on the incidence of PCR-detected *Plasmodium falciparum* malariaTo estimate the protective efficacy of ETUs plus DEET lotion compared to untreated uniforms and placebo lotion on the incidence of PCR-detected *Plasmodium falciparum* malaria infection, i.e. the protection of etofenprox-treated clothing with DEETTo estimate the compliance of personnel with the system of tropical environment protection

### Trial design {8}

#### Study design

The trial is a four-arm cluster randomised double-blind placebo-controlled study. The unit of randomisation is the company, or *combania.* A combania is a military subsection of recruits who carry out all activities together and sleep in the same dormitory.

## Methods: participants, interventions and outcomes

### Study setting {9}

The trial will take place at Mgambo National Service Camp in Kiswahili Jeshi la Kujenga Taifa (JKT) military camp in Tanga region. Tanga is on the east coast of Tanzania, 250 km north of the commercial capital of Tanzania, Dar es Salaam. The climate is tropical, with temperatures of 21 to 33 °C during the hottest period (November to February) and 20 to 30 °C in the cooler period (May to August). The rainfall seasons are bimodal, with shorter rains from October to December and longer rains from March to May. The prevalence of malaria infection among recruits determined by a rapid diagnostic test (RDT) is about 30% [21].

### Eligibility criteria {10}

#### Study participants

Healthy recruits of the Tanzanian National Service Program JKT aged 18 to 25 who meet the trial inclusion criteria (Table 1) and who are enrolled into the trial upon written informed consent. Any participants who do not attend the screening for more than 2 months will be assumed to have dropped out. This may be due to deployment to another area or expulsion for misconduct.

**Table 1 Tab1:** Inclusion, exclusion and withdrawal of trial participants

Inclusion criteria	Exclusion criteria	Withdrawal criteria
New recruits to national service JKT at Mgambo and do not use any malaria prophylaxis	**Already employed military personnel	Participants who wish to use malaria prophylaxis in parallel with intervention provided
Member of a *combania	Not assigned to a combania	Participants who do not reside in combania dormitories
Passes physical examination—no underlying health risks	Underlying health risks—does not pass the physical examination (No recruits to JKT are accepted if they have chronic health problems.)	Acquired illness or physical condition that makes a participant permanently not involved in military instructions
Recruits who are not pregnant	(Pregnant people are not recruited to JKT.)	Participant known to have become pregnant
Consents to participate	Does not consent to participate	Withdraws consent to participate

*Recruits are grouped into companies, or *combania*, which will be the level of randomisation

**Employed military personnel are combat ready and can be deployed at any time to any mission. National service members are available for at least a year and are not involved in combat missions

### Who will take informed consent? {26a}

Before enrolment, the aims of the study and study procedures will be explained to the participants, along with their right to withdraw from the study at any time. People who agree to enrol in the study will sign a consent form. Interviewers will be trained on the elements of informed consent and on the interviewing technique to respect the dignity and privacy of participants. Non-military staff will conduct all data collection to prevent potential coercion by military staff. Any person not willing to participate will be provided with standard untreated uniforms and will not be followed up.

### Additional consent provisions for collection and use of participant data and biological specimens {26b}

After PCR testing for *Plasmodium falciparum*, blood spots will be destroyed by incineration.

### Interventions

#### Explanation for the choice of comparators {6b}

The trial will use PTUs in combination with DEET as an active comparator to ETUs with DEET because PTU plus DEET is the existing personal protection method most widely used by the military globally. Untreated uniforms with placebo DEET will be a placebo comparator group to examine the absolute protective efficacy in the PTU-with-DEET and ETU-with-DEET study arms. This provides an opportunity to examine these two intervention systems simultaneously in a randomised control trial for the first time. The use of PTU without DEET will allow the evaluation of any additional protective benefit of using DEET.

#### Intervention description {11a}

Each participant will receive two uniforms, both treated according to the treatment arm. The uniforms will be impregnated with insecticide at Warmkraft–Pine Belt Processing Inc. Participants will wear one of the uniforms all day every day. The second uniform will be worn when the first is being washed. The insecticide in the uniforms will still be viable even after 50 washes [22–24].

##### PTU

No adverse health risks are known to be associated with wearing PTUs. Safety testing of permethrin has been ongoing since the 1970s, following its US Environmental Protection Agency (EPA) registration for use in a variety of applications, including food crops, animal feed crops, livestock, public health mosquito abatement programmes, pets and clothing [25]. Permethrin was first registered for use as a repellent on military clothing in 1990 and is the only insect repellent currently used for factory treatment of clothing. It is a broad-spectrum, non-systemic, synthetic pyrethroid insecticide that targets adults and larvae of many species of biting insects. The EPA has determined that wearing or coming in contact with PTUs for 250 days a year is unlikely to cause adverse health effects [12]. The objective is to provide 90% bite protection for at least 50 launderings, an objective easily met through factory treatment of the army combat uniform (ACU) with permethrin, which demonstrates 99 to 100% bite protection for up to 50 launderings [26].

##### ETU

No adverse health risks are known to be associated with wearing etofenprox-treated clothing. Etofenprox has now received EPA registration for use on military uniforms. The WHO dermal risk assessment for etofenprox is based on a no-observed-adverse-effect level (NOAEL) of 2100 mg/kg/day, which is four times greater than that of permethrin. Uniforms will be factory treated with 0.9% etofenprox. When compared to untreated control fabric, etofenprox-treated fabric demonstrated greater than 90% bite protection after 3 washes [27] and has already been approved for use by US Army personnel.

##### DEET

Each participant from a combania that receives DEET will be given a 120-mL container of 30% DEET repellent (Lipo DEET) for topical application, and the container will be replaced every 2 weeks. Combania in placebo arms will be given 120 mL of placebo lotion. The DEET lotion and its placebo will be prepared by Sawyer Ultra 30. Participants will be instructed to apply the repellent topically twice daily: once in the morning and once in the evening. One application of Lipo DEET protects for up to 12 h and has a pleasant odour and non-greasy feel on the skin. This liposome-based repellent is the newest advance in insect repellent technology. Like the earlier generation of polymer-based controlled release systems, the liposome envelops the active ingredient, DEET, and slowly releases it as needed, thereby extending the repellent’s effectiveness. DEET was selected for this study because it has been extensively tested for safety and toxicity for human use [28–30] and for its efficacy against a broad variety of arthropod vectors [31–33]. DEET was first registered in 1957 and has an excellent safety profile [34, 35].

### Criteria for discontinuing or modifying allocated interventions {11b}

There are no plans to discontinue or modify the interventions. Follow-up is planned for 12 months to include the bimodal rainfall seasons, which affect mosquito abundance and malaria transmission. It is likely to be difficult to demonstrate futility without the full data set due to year-to-year variation in the seasonal pattern. Issues of safety are not expected because the products are already approved. In the case of severe adverse reactions, individual participants will be withdrawn from the trial.

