#### Concealment mechanism {16b}

Manufacturers of the uniforms and repellents will prepare active and placebo uniforms and repellent and placebo lotions in identical containers identifiable by a 6-digit code sewn into the uniform or applied on the lotion bottle. Each combania will be allocated an identification code. There will be one code per combania, to limit the effect of accidental unblinding, and a separate code for additional untreated uniforms and placebo DEET, in case of adverse events.

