#### Procedure for unblinding if needed {17b}

In the advent of a severe adverse event thought to be connected to the intervention, the recruit will be allocated untreated uniforms. The time contributed to the study by a person who experienced an adverse event will be included in the intention-to-treat analysis. Unblinding of the participant will be carried out if necessary to allow the study doctor to provide appropriate care. Only the study doctor will be informed of the person’s intervention allocation; other participants and investigators will remain blinded. The IHI Institutional Review Board will be informed of the adverse event.

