#### Defining compliance

Compliance with the intervention will be estimated as the proportion of 2-week time intervals where the participant was compliant and estimated by study arm and over time. The JKT recruits must wear uniforms and will be provided with two treated uniforms. They have no alternative clothing, leading to an expected 100% compliance; compliance with clothing will not be monitored. Participants’ repellent bottles will be weighed twice weekly to estimate application rates. If a bottle contains more than 50% of the required dose, the participant will be recorded as non-compliant.

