#### Adverse event reporting and harms {22}

The team physician will determine the relationship between any adverse event and the intervention. All adverse events will be treated as clinically indicated, and subsequent treatment will be recorded. If necessary, participants will be referred for special care at the local hospital. Study clinicians who determine that an AE/SAE (adverse event or severe adverse event) is intervention related and that stopping intervention is clinically indicated will stop the study intervention. All adverse events will be reported to the IRB. Adverse events will be recorded, and descriptive analysis of adverse events will be reported as part of the publication arising from the trial.

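### The protocol handles a severe product-related reaction inconsistently, so it is unclear whether the recruit's trial data continue and how time after a product switch is analysed

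*Protocol article*

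**What the plan says.** Five places in the Protocol article bear on a recruit who reacts severely to a study product.

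- **Criteria for discontinuing or modifying allocated interventions {11b}:** "In the case of severe adverse reactions, individual participants will be withdrawn from the trial". No exception or discretion is attached.
- **Procedure for unblinding if needed {17b}:** here the product is replaced instead. The rule reads "In the advent of a severe adverse event thought to be connected to the intervention, the recruit will be allocated untreated uniforms". On the analysis, the same section then adds a second rule: "The time contributed to the study by a person who experienced an adverse event will be included in the intention-to-treat analysis". Only the study doctor may learn the allocation. Lotion is not mentioned.
- **Concealment mechanism {16b}:** the supplies include "a separate code for additional untreated uniforms and placebo DEET, in case of adverse events".
- **Adverse event reporting and harms {22}:** clinicians who judge an event related and "that stopping intervention is clinically indicated will stop the study intervention". Leaving the trial is not mentioned.
- **Eligibility criteria {10}, Table 1:** no withdrawal criterion is an adverse reaction. The nearest entry is "Acquired illness or physical condition that makes a participant permanently not involved in military instructions".

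Two analysis sections then matter. Statistical methods {20a} makes intention to treat primary. Its per-protocol analysis removes two-week periods for three reasons only: lotion non-compliance, antimalarial use and personal travel. Defining compliance assumes full uniform compliance, says "compliance with clothing will not be monitored", and judges lotion compliance by bottle weight.

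**The concern.** One event meets several instructions, and they lead to different data. Under {11b} the recruit leaves the trial. Under {17b} and {16b} the recruit appears to carry on with replacement products. Under {22} the product may or may not be stopped, and nothing is said about follow-up.

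Two things are at stake:

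- **Intention to treat.** Withdrawal from the trial removes outcome data because of something the product did. A reaction to an insecticide or to DEET cannot arise in the untreated-uniform, placebo-lotion arm, and the insecticide differs between the two primary arms. The loss can therefore depend on arm.
- **Per protocol.** If the recruit is switched and stays in, no exclusion in {20a} catches the change. A recruit in an untreated uniform who uses up the placebo lotion issued would be analysed as compliant with an active arm.

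**Working it through.** The protocol gives no figure for this point, so there is none to reproduce. The first two steps compare text. The last two illustrate size under assumed values.

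**1. Can the rules be read as one?** The best attempt reads {17b} as handing an untreated uniform to someone who has left the trial, with the time counted being time before leaving. Who will take informed consent? {26a} gives untreated uniforms to people who are not followed up, which fits. But {16b} also reserves coded placebo lotion for adverse events, and someone who has left a trial has no use for it. {17b} also keeps other participants and investigators blinded. These provisions suggest continued participation, which {11b} rules out. The conflict stands.

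**2. What happens to the data under each reading?**

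| Reading | Two-weekly qPCR and questionnaire | Intention to treat | Per protocol |
|---|---|---|---|
| Withdrawn ({11b}) | Not stated to continue | Later time lost | Later time lost |
| Switched and stays in ({17b} with {16b}) | Presumably continue | Later time could count | Later time counts as compliant if the lotion is used |
| Product stopped on judgement ({22}) | Not stated | Not stated | Depends on whether bottles are still weighed |

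**3. Person-time affected.** Sample size {14} gives about 480 recruits per primary arm and 12 months of follow-up, so 480 person-years. Assume 1% to 5% of an arm react, on average at mid-year.

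- Recruits: 480 × 0.01 = 4.8 (about 5) to 480 × 0.05 = 24.
- Person-years: 4.8 × 0.5 = 2.4 to 24 × 0.5 = 12, which is 0.5% to 2.5% of 480.

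**4. Effect on the primary incidence rate ratio (IRR) if recruits are withdrawn.** From the inputs in {14}, the permethrin-plus-DEET rate is 0.68 × (1 − 0.5 × 0.8) = 0.408 and the etofenprox-plus-DEET rate is 0.68 × (1 − 0.7 × 0.8) = 0.299, so IRR = 0.733. The protocol prints 0.27 and 0.66 for the last two. That is a separate matter and does not change the conclusion here.

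Take a one-sided case: a fraction f of the etofenprox arm is withdrawn at mid-year and nobody in the comparator arm. Let k be their malaria risk relative to the rest, and λ = 0.2992 / (1 − f + f·k). Then

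observed rate = λ × [(1 − f) + 0.5·f·k] / [(1 − f) + 0.5·f], and IRR = observed rate / 0.408.

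| f | k = 1 | k = 1.5 | k = 2 |
|---|---|---|---|
| 1% | 0.733 | 0.732 | 0.730 |
| 2% | 0.733 | 0.730 | 0.726 |
| 5% | 0.733 | 0.725 | 0.716 |

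The largest shift is 0.733 − 0.716 = 0.017. This keeps each recruit's risk constant over the year. If risk after stopping instead returned to 0.68, the missing time matters in the other direction. At f = 5% the rate with all time counted would be 0.975 × 0.2992 + 0.025 × 0.68 = 0.3087, giving 0.3087 / 0.408 = 0.757, a difference of 0.023. Either shift is small beside the confidence interval of 0.49 to 0.88 that {14} expects.

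**The case against.** The strongest reply is that this is one untidy phrase in a condensed article, about an event the protocol does not expect. Much of that reply limits the point.

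- **Inclusion after a switch.** A reader might infer that {17b} keeps switched recruits in the analysis afterwards. The text does not say so: time contributed may mean time before leaving. The per-protocol problem is therefore conditional on recruits staying in.
- **Lotion reactions.** Because {17b} names only the uniform, a reader might infer that someone reacting to the lotion must stay on it. The document does not require that: {22} lets clinicians stop the intervention. Nor is the reserve stock in {16b} a rule that both products are always replaced.
- **Safety information.** A reader might infer that the course of the reaction goes unseen. {22} has events treated, the treatment recorded and the ethics board told, and Provisions for post-trial care {30} adds hospital transport and insurance. What no section says is that trial assessments continue.
- **Uniform adherence.** It is not wholly unmeasured: Strategies to improve adherence {11c} includes a two-weekly question on it. No per-protocol exclusion uses the answer.
- **Lotion stopped.** If lotion is stopped and bottles are still weighed, that time falls out as non-compliant.
- **Size.** The 1% to 5% rate is an assumption. Both primary arms receive DEET, so between them only uniform reactions could differ by product.

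It does not remove the point. The sections contradict each other in the current text, so this is not detail left to a fuller document, and the reserved placebo lotion cannot be squared with withdrawal from the trial.

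**Conclusion.** The point holds as an inconsistency with a conditional consequence. Sections {11b}, {16b}, {17b} and {22} and Table 1 do not give one answer for a severe product-related reaction. Read literally, {11b} ends two-weekly outcome data for those who react, in a way that can depend on arm and works against the stated primary analysis. If recruits are switched, stay in and use the placebo lotion, their later time is misclassified in the per-protocol analysis.

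The number affected is unknown. Under the assumed 1% to 5% it is at most 2.5% of an arm's person-time, and the primary IRR moves by about 0.02 at most in the one-sided cases shown. A reader might infer material bias in the main result; the documents do not support that. The reasons to correct it are consistent handling and complete data for the recruits whose experience matters most for safety, in a trial without a data monitoring committee ({21a}).

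**What to change.** 1. Reconcile {11b}, {16b}, {17b}, {22} and Table 1 into one consistent statement. Which products are stopped or replaced, on whose decision, and how the event is managed are for the sponsor to decide.
2. State that stopping or replacing a product does not by itself end trial data collection. Two-weekly sampling and questionnaires continue unless consent is withdrawn, and the recruit is analysed by randomised combania.
3. Say in {17b} whether time after a switch counts in the intention-to-treat analysis.
4. Record the date of any stop or switch, and add time after it to the per-protocol exclusions in {20a}.

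The cost is protocol wording, one date field and one more exclusion. The visits are already scheduled for everyone in the trial, and Trial status says recruitment had not begun.
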